**Fig. 1 Fig1:**
[figure not shown]
Flow diagram of the progress from screening to the final follow-up assessment

### Intervention

#### Exercise program

All participants involved in the study will be prescribed an individually tailored and supervised aerobic, PRT and challenging balance and mobility program. All training will be conducted at local community health and fitness centres and participants will be asked to train on three non-consecutive days per week for 24 weeks. Each training session will last approximately 60–75 minutes, and include: a warm-up and cool-down, 15–20 minutes of moderate intensity [5 to 8 (‘somewhat hard’ to ‘hard’) on the 10 point Borg Rating of Perceived Exertion (RPE) scale] aerobic training (e.g. cycling, treadmill walking, stepping), at least two challenging balance/mobility and postural exercises, and 30–40 minutes of moderate to high intensity PRT. All exercise sessions will be supervised by qualified exercise trainers and will be conducted in small groups where possible (approximately 6–8 per group), but each participant’s program will be individualised. For the first two weeks, participants will be asked to complete three sets of 12–15 repetitions for each resistance exercise using relatively moderate resistance to familiarize themselves with the equipment (free and machine weights), the training protocol, and the correct execution of the exercises. Thereafter, participants will be asked to complete three sets of 8–12 repetitions for at least eight different upper and lower body exercises at an intensity corresponding to 5 to 8 (‘somewhat hard’ to ‘hard’) on the 10 point Borg RPE scale. Some examples of the exercises that will be used throughout the program include: squats, lunges, box step-ups, leg extensions, standing leg curls, hip abductions, calf raises, shoulder press, upright row, bicep curls, wall push-ups, and triceps kickbacks/pushdowns. Where possible, all exercise sessions will be conducted prior to lunch or dinner so that the participants can consume their prescribed meal type as soon as possible following the training. If this is not possible, participants will be instructed to consume one serve of red meat before training or both serves after a training session.

#### Lean red meat

Participants allocated to the red meat group will be supplied with ~220 g (raw weight) of lean red meat to be consumed on each of the three training days per week for 24 weeks to achieve a modest increase in mean dietary protein intake in mean dietary protein intake to a level of at least 1.3 g/kg/day. This equates to ~160 g of cooked meat per day (~45 g of protein). All participants will be asked to prepare the meals themselves and consume the meat at lunch and dinner (~80 g cooked serving per meal) as there is emerging evidence that a divided dose of protein spread throughout the day may be more effective for enhancing muscle protein synthesis than a single large dose in the evening [49]. The meat will be supplied in labelled 110 g portion packs trimmed of visible fat, and participants will select from a variety of veal, lamb or beef cuts, delivered frozen every 4 weeks by a local butcher. Participants living with a partner will also receive sufficient food supplies for their partner. For the other non-training days, participants will be advised to maintain their usual diet. All participants will be provided with instructions of how to maintain a daily protein rich diet (e.g. foods and recipes rich in protein) and will receive recipes and written dietary instructions for consuming the red meat. We have found that this dietary intervention in older women results in a modest average increase in dietary protein from 1.1 to 1.3 g/kg/day [15]. We therefore expect that participants will achieve an intake of approximately 1.3 g/kg/day for 3 days/week when exercising and around 1.1 g/kg/day for the remaining 4 days.

#### Carbohydrate control

Participants randomized to the carbohydrate control group will be instructed to consume their usual diet and consume at least one serving per day of carbohydrates (rice, potato and pasta) on each of the training days. As all adults consume some carbohydrate foods every day the provision of rice/pasta is provided to assist in keeping the participants’ dietary protein intakes towards the lower range of usual intake (<1.1 /kg/day) and to ensure that both groups receive the same level of attention. Participants in this group will be supplied with packs of pasta and rice every 3 months, and advised to consume at least one serving (~1/2 cup or ~125 ml) of cooked rice or pasta or potato on the training days (~25–35g of carbohydrates), and to focus on having larger servings of bread, cereals, rice and vegetables and smaller serves of protein foods (e.g. meat and fish). We have previously found that the provision of some rice and pasta together with this dietary advice results in no significant change in mean dietary protein intake, which remained at 1.1 g/kg/day in older women [15]. All participants will be provided with recipes and written dietary instructions for consuming a carbohydrate-rich diet and supplies for their partner where appropriate.

#### Vitamin D

All participants will be asked to take one 1000 IU vitamin D_3_ capsule (Ostelin, Australia) per day to try to ensure that serum 25-hydroxyvitamin D concentrations are ≥50 to 60 nmol/L for all participants, which is the current recommended level for Australian adults [50].

### Follow-up

At the completion of the 24-week supervised and structured intervention, all participants will be encouraged to continue to participate in the exercise program (at their own expense) and those in the red meat group will be asked to continue to consume a protein-rich diet with at least three servings of red meat per week. The primary aim of the follow-up period is to document any long-term behavioural changes with regard to maintaining participation in regular exercise and consuming a diet rich in red meat. All participants will be contacted via the telephone at weeks 36 and 48 to assess their exercise and dietary habits, using the similar methodology of 24 hr dietary recalls and a questionnaire specifically targeting the consumption of dietary protein including intake of red meat over the defined period of time since last contact.

### Outcome measures

A summary of the primary and secondary outcomes and other relevant covariates is shown in Table 1. All participants will be asked to attend Deakin University at baseline and week 24 to undertake testing, with an intermediary assessment of cognitive function conducted on-site at each health and fitness centre at week 12. With the exception of the fasted blood samples which will be collected at local pathology clinics, and the intermediary assessment, all other outcome measures will be assessed within the Centre for Physical Activity and Nutrition Research within the School of Exercise and Nutrition Sciences at Deakin University, Burwood, Melbourne, Australia.

**Table 1 Tab1:** Summary of the outcome measures

Variables	Data collection method	Data collection points (weeks)				
Primary outcome measures	Baseline	Baseline	12	24	36	48
Muscle mass and cross-sectional area	Dual energy X-ray absorptiometry (DXA) total body and regional lean mass	x		x		
	Peripheral quantitative computed tomography (pQCT) scan at 25% femur site	x		x		
Muscle strength	Leg press	x		x		
	Isometric knee extensor strength	x		x		
Cognitive function	Cogstate Brief Battery computerized tests	x	x	x		
	Behaviour Rating of Inventory of Executive Function-Adult Version (BRIEF-A)	x		x		
Secondary Outcome Measures						
Muscle Function	Four-square step test	x		x		
	4 meter walk	x		x		
	30-second sit-to-stand test	x		x		
	Timed up and go test	x		x		
Fat mass and inter-/intra-muscular fat	DXA (total body and regional) and pQCT (25% femur site)	x		x		
Biochemistry and hormonal measures	Overnight fasted blood collection	x	x	x		
Neurotrophic markers	Overnight fasted blood collection	x	x	x		
Adipokines and Inflammatory markers	Overnight fasted blood collection	x	x	x		
Blood lipids	Overnight fasted blood collection	x	x	x		
Bone mineral density	DXA total body, hip and spine scan	x		x		
Blood pressure	Automated measurement	x		x		
Health related Quality of Life	Short form (SF)-36 version 2 questionnaire	x		x		
Neural plasticity and voluntary activation	Transcranial Magnetic Stimulation (TMS) *	x	x	x		
Additional Measures						
Anthropometry	Height, weight and body mass index (BMI)	x		x		
Health and Lifestyle information	Lifestyle Questionnaire	x		x		
Habitual physical activity	Community Healthy Activities Model Program for Seniors questionnaire	x		x	x	x
Memory and mood	Memory Assessment Questionnaire (MAC-Q)	x		x		
Depression and anxiety	The Hospital Anxiety and Depression Scale (HADS) questionnaire	x		x		
Diet	24-hour food diaries	Monthly			x	x
Compliance to red meat and carbohydrates	Food records	Daily calendar				
Vitamin D supplement compliance	Pill count			x		
Compliance to exercise program	Exercise cards	Monthly				
Adverse events	Exercise cards and adverse events form	Monthly				

* TMS will also be assessed at week 4 and 8

#### Primary outcome measures

The primary outcome measures will be changes in total body and regional (leg) lean tissue mass and muscle cross-sectional area, muscle strength and cognitive function.

##### Body Composition

Dual energy x-ray absorptiometry (DXA) will be used to assess total body and regional (arms and legs) lean tissue mass, fat mass and percentage body fat (Lunar Prodigy, GE Lunar Corp., Madison WI, software version 12.30.008). Muscle cross-sectional area and muscle density, as a surrogate measure of inter-/intra-muscular adiposity, at the 25 % femur site will be assessed using peripheral quantitative computed tomography (pQCT) (XCT 3000, Stratec Medizintechnik GmbH, Pforzheim, Germany). As previously reported [15], after performing a scout view of the distal end of the femur, scans will be placed at the 4 % and 25 % position of the femur. Slice thickness will be 2.3 mm, and voxel size will be set at 0.3 mm with a scanning speed of 10 mm/s. Subcutaneous fat CSA will be determined by selecting the area with thresholds –40 to +40 mg/cm^3^ HA density (contour mode 3, peel mode 1), and muscle CSA will be determined by subtracting the total bone CSA (threshold, 280 mg/cm^3^; contour mode 1, peel mode 2) and subcutaneous fat CSA from the total area of the distal femur (threshold, –40 mg/cm^3^, contour mode 3, peel mode 1). The short-term co-efficient of variation (CV) for repeated measurements of total body lean mass and fat mass in our laboratory ranges from 1.0 % to 1.7 %. The CV for femur muscle CSA is 1.3 %.

##### Muscle strength

Lower limb muscle strength will be measured from the leg press machine using a three-repetition maximum strength (3-RM) protocol. The 3-RM is the heaviest weight that an individual can complete three repetitions of an exercise whilst maintaining correct form and technique, which corresponds to ~85 % of an individual’s one repetition maximum strength (1-RM). Prior to the assessment of each individual’s 3-RM leg press strength, they will be required to complete a 5-minute warm-up on an exercise bike. To determine 3-RM, each participant will perform a warm-up set of 8-10 repetitions with a light to moderate load. After the successful completion of a further 6–8 repetitions at a heavier weight selected by the instructing researcher and following a brief rest (~1–2 minutes), the weight will be increased incrementally until only three repetitions with correct technique can be completed. To calculate 1-RM strength, the formula developed by Wathen et al. [51] will be used. In addition to the leg press, isometric knee extensor strength will be measured on the participants’ dominant leg using Lord's strap assembly incorporating a strain gauge (Neuroscience Research Australia, Sydney, Australia). Participants will have one practice trial followed by two maximal tests with a 60 second rest between each test. This test has been shown to have excellent test-retest reliability (Pearson r=0.92) [52]. For analysis, knee extension strength (kg) will be expressed per unit of lower leg length to compensate for the length of the lever arm.

##### Cognitive function

The CogState Brief Battery computerized tests (http://cogstate.com/) will be used to assess cognitive function at baseline, 12 and 24 weeks. Briefly, this is a multi-task computerised battery which provides sensitive and valid measurement of a range of different cognitive functions [53–55], including attention, processing speed, memory and executive function. It is designed to assess cognition over serial time points using a computerised system that takes 30–40 minutes to complete depending on the number of tests used. Importantly, it has been specifically designed for repeated administration over short time periods and has been validated in older adults, with minimal practice or fatigue effects, making it suited for detecting subtle change [53–55]. For this study, participants will be asked to complete five tasks from the CogState battery on a laptop with a mouse and headphones provided. Prior to each test, participants will be given a verbal set of instructions, reinforcing the instructions written on the screen. Participants will also be given a practice to ensure that they understand what is required for each test. A brief description of the five tasks is provided below.The *Groton Maze Learning Task (GMLT)* is a test of executive function, memory and spatial problem solving. In this test, participants will be exposed to a 10 x 10 grid of tiles on a computer screen, with a 28-step pathway hidden among the 100 possible locations. Participants will be required to find the hidden pathway (through trial and error feedback) that extends from one corner of the grid to the other, and remember (repeat) this pathway for four subsequent trials. The task is scored using the total number of errors made by the participant on five consecutive trials at a single session. The lower the score, the better their performance.The *Detection Task (DET)* is a test of reaction time measuring psychomotor function and speed of processing. In this task, participants will be shown the back of a playing card (patterned side) in the centre of the screen and asked to respond to the question “has the card turned over yet? As soon as the card is flipped to the picture side, participants will be required to press ‘yes’ on the keyboard as quickly as possible. The task is completed after 35 correct trials have been recorded. This task is scored using speed in milliseconds. The average reaction times for correct responses will be used, normalised using a log10 transformation.The *Identification Task (IDN)* is a test of choice reaction time measuring visual attention. For this task, participants will be shown the back of a playing card in the centre of the screen, and asked to respond to the question ‘is the card red?” As soon as the card is flipped to the picture side, the participants have to decide as quickly as possible whether the card is red or black. If the card is red, participants will press the ‘yes’ key. If the card is black, they will press the ‘no’ key. The task will end after 30 correct responses have been recorded. The task is scored using speed in milliseconds and mean reaction times for correct responses. The average will be normalised using a log10 transformation.The *One Card Learning Task (OCLT)* is a test assessing visual recognition memory and attention. In this task, participants will be shown the back of a playing card in the centre of the screen and asked to respond to the question “have you seen this card before in this task?” If the participant has seen the card, they will be required to press the ‘yes’ key, or the ‘no’ keys if they have not. In this task, six cards are randomly drawn from the deck and repeated throughout the task, and the first response will always be ‘no’, as there has been no previous card shown to the participant in the task. This task will end after 88 trials, and is scored using the proportion of correct responses, using an arcsine square-root transformation to normalise the data.The *One-Back Working Memory Task (OBWMT)* is a test assessing working memory and attention. In this task participants will be shown the back of a playing card in the centre of the screen, and asked to respond to the question “is this card the same as that on the immediately previous trial?” If the answer is yes participants will be required to press the ‘yes’ key, or the ‘no’ key if the card is not the same. The first response in this task is always ‘no’ as there is no card prior to the first card. The task will end after 30 correct responses have been recorded. This test is scored using the proportion of correct responses, using an arcsine square-root transformation to normalise the data.

As previously reported [56], composite variables will be created using each individual variable within a cognitive domain. Scores will be transformed into a z-score using the mean and standard deviation (SD) of the total sample in the study and these z-scores will be averaged across tests resulting in a single composite score for processing speed/attention, memory and executive function for each participant. Higher scores on these composites indicate better performance and cognitive function.

Participants will also be required to complete a self-report of executive function at baseline and week 24 using the Behaviour Rating of Inventory of Executive Function-Adult Version (BRIEF-A). This is a self-report measure comprised of 75 questions that make up nine non-overlapping theoretically and empirically derived clinical scales that provide a measure of various aspects of executive functioning. These scales include: inhibit, self-monitor, plan/organize, shift, initiate, task monitor, emotional control, working memory, and organization of materials [57]. For each question, a response of never, sometimes or often will be recorded for how often in the last month each behaviour listed had been a problem. Each response corresponds to a number score of 1 to 4, and these are summed to provide scores for each subdomain. The inhibit, shift and emotional control subdomains are summed together to provide a behavioural regulation index (BRI) score and the other subdomains are summed to provide a metacognition index score (MI) [57]. Lastly, the BRI and MI can be summed to provide an overall global executive composite (GEC) summary score [57].

#### Secondary outcome measures

Secondary outcome measures to be assessed at baseline and week 24 (unless stated otherwise) will include: changes in fat mass, muscle function, various circulating biochemical, growth, inflammatory and neurotrophic markers, bioavailable zinc, corticospinal excitability and inhibition, blood pressure, blood lipids, memory, mood, anxiety/depression, health-related quality of life and adverse events. Other covariates and variables of interest to be assessed include: anthropometry, habitual physical activity, diet, alcohol intake and smoking status and medication use. A summary of all the outcome measures is shown in Table 1.

##### Biochemical, hormonal and inflammatory markers

All participants will be asked to attend one commercial pathology clinic with multiple collection centres where a fasted, morning (8–10am) venous blood sample will be collected at baseline, 12 and 24 weeks. All blood will be sent to a central laboratory that is a National Association of Testing Authorities Royal College of Pathologists Australasia accredited pathology laboratory. Serum total cholesterol, high-density lipoprotein (HDL)-cholesterol and triglycerides will be determined using an enzymatic colorimetric method (Roche Diagnostics, Mannheim). Low density lipoprotein (LDL)-cholesterol will be calculated by using Friedewald’s formula. High sensitivity C-reactive protein (hs-CRP) will be measured by an Immunoturbidimetric assay from Roche Diagnostics, Mannheim. Serum creatinine, urea, albumin, calcium, phosphorus, sodium, potassium and phosphorus will be analysed by using standardized techniques. A 24-hour urine sample will be collected and analysed for urinary urea, creatinine, potassium and sodium using standard techniques. Glomerular filtration rate (eGFR) will be calculated using the participants’ serum creatinine, age and gender in accordance with the appropriate Chronic Kidney Disease Epidemiology Collaboration (CKD-EPI) formula as outlined by Johnson et al [58].

Serum aliquots will also be collected and stored at –80 °C so that the following parameters can be assessed in a single batch at the completion of the study: serum IGF-1, 25-hydroxyvitamin D, homocysteine, vitamin B_12_, folate, BDNF, vascular endothelial growth factor (VEGF), adiponectin and a battery of pro-inflammatory and anti-inflammatory cytokines, including interleukin-6 (IL-6), interleukin-1 beta (IL-1β), interleukin-8 (IL-8), tumor necrosis factor-alpha (TNF-α) and interleukin-10 (IL-10). Serum bioavailable zinc will also be measured using flame atomic absorption spectrophotometry by direct aspiration (Varian SpectrAA-800).

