There are several lines of evidence to support our hypothesis. One of the proposed mechanisms by which exercise may improve cognition and neural plasticity as well as muscle health is via an increase in circulating IGF-1 and serum brain-derived neurotrophic factor (BDNF) and/or a reduction in systemic inflammation [40, 41]. It is well known that IGF-1 is central to muscle growth, but it has also been shown to have neuroprotective actions by promoting neuronal growth, survival and differentiation [40, 42]. IGF-1 has also been shown to augment BDNF concentrations, which is a neurotrophin that functions to support the growth and maintenance of neuronal circuits as we age [40]. Indeed, a number of human studies have reported a link between circulating BDNF concentrations and cognition [43, 44], and there is evidence that BDNF stimulates neurons to survive longer and branch and connect in new ways (synaptic plasticity) to promote memory and learning [40, 45] as well as executive function and processing speed [44, 46]. Finally, increased inflammation has also been linked to muscle loss and cognitive impairment, and associated with an increased risk of dementia [47, 48]. Building upon our previous 4-month randomised controlled trial in elderly women which showed that PRT combined with increased consumption of lean red meat on most days of the week resulted in a greater increase in serum IGF-1 and a reduction in circulating IL-6 levels compared to PRT alone, together with existing research which has shown that dietary protein and exercise can stimulate an increase in serum BDNF, we hypothesise that combining these approaches will be more effective at improving cognitive performance in older adults than exercise alone. In addition, by measuring changes in cortical plasticity using Transcranial Magnetic Stimulation (TMS), a painless and non-invasive technique that allows an assessment of neuroplasticity through cortical excitability and inhibition (eg. responsiveness of the entire neural pathway from the motor cortex to the muscle), this study will provide new data on the role of PRT combined with increased dietary protein on neural plasticity in the elderly.

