#### Screening and eligibility

Screening will consist of a four-step process. First, all participants will be screened over the telephone and deemed ineligible based on the following criteria: 1) aged <65 years; 2) current or prior participation in resistance exercise (>1 day per week) and/or moderate-intensity physical activity ≥150 minutes per week in the past 3 months; 3) acute or terminal illness, including current (treated or untreated) cancer or surgery/cessation of chemotherapy/radiotherapy less than 12-months ago; 4) history of a recent low trauma fracture with functional impairment that would limit participation in the exercise program; 5) body mass index (BMI) >40; 6) use of insulin to treat diabetes; 7) chronic liver disease, coeliac or inflammatory bowel disease, including ulcerative colitis or Crohn’s disease; 8) recent use of oral corticosteroids (past 6 months); or 9) inability to commit to the study and its requirements. Participants will not be excluded if they are currently taking vitamin D supplements, but will be asked to take the vitamin D that is provided to them as part of the study so that we are able to monitor compliance. Second, eligible participants will then be asked to complete the Short Portable Mental Status Questionnaire (SPMSQ) and the Geriatric Depression Scale (GDS) to evaluate whether they are cognitively healthy and have no signs of depression. Those with a score of greater than two on the SPMSQ and/or a score of greater than six on the GDS will be excluded from the study. For these participants, a letter will be sent to their doctor and they will be encouraged to make an appointment with them to discuss this is in further detail. Participants that remain eligible will then be required to obtain approval from their local doctor to clear them of any contraindicated medical conditions to exercise, based upon American College of Sports Medicine (ACSM) guidelines, to participate in the program. Finally, participants will be asked to provide a fasted, morning blood sample to confirm that their estimated Glomerular Filtration Rate (eGFR) is >45 mL/min/1.73m^2^. Written informed consent will be obtained from all participants prior to commencing the program.

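### Week 12 and 24 blood draws are fixed by fasting and clock time but not by time since the last session or supplied meat, which adds avoidable timing variation to the secondary markers

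*Protocol article*

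**What the plan says.** All statements are from the protocol article.

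- **Blood draw** (Biochemical, hormonal and inflammatory markers): a "fasted, morning (8–10am) venous blood sample will be collected at baseline, 12 and 24 weeks". One pathology provider, a central laboratory and single-batch analysis of the stored aliquots are also specified. Neither this section nor Table 1 ties the draw to a session or a study meal.
- **Training** (Exercise program): "All participants involved in the study will be prescribed an individually tailored and supervised aerobic, PRT and challenging balance and mobility program", and "participants will be asked to train on three non-consecutive days per week for 24 weeks". Where possible, "all exercise sessions will be conducted prior to lunch or dinner so that the participants can consume their prescribed meal type", so an evening session before a next-morning draw is allowed.
- **Diet on training days**: the meat arm is to "consume the meat at lunch and dinner (~80 g cooked serving per meal") (Lean red meat). The control arm is to "consume at least one serving per day of carbohydrates (rice, potato and pasta) on each of the training days" (Carbohydrate control).
- **Before baseline** (Screening and eligibility): the exclusion is for "current or prior participation in resistance exercise (>1 day per week) and/or moderate-intensity physical activity ≥150 minutes per week in the past 3 months".
- **Use of the markers**: they are secondary outcomes. Under Statistical analyses, intervention effects come from linear mixed models, and a separate multiple regression relates circulating markers to change in cognition. That regression serves an exploratory secondary aim stated in the Background.

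**The concern.** The sampling conditions leave out the one condition that the intervention itself changes. Before baseline nobody has had a study session or a supplied meal. At weeks 12 and 24 some samples will be taken the morning after one and some will not, with nothing to keep the mix constant between people or visits.

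The article gives some reason to think this could matter: it cites "existing research which has shown that dietary protein and exercise can stimulate an increase in serum BDNF". That statement covers BDNF only and does not separate a short-lived response from a lasting one.

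Three uses of the data are exposed to different degrees:

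- **Within-arm change from baseline** can mix the last bout with the 24-week adaptation.
- **The marker–cognition regression** is not protected by randomisation, and variable timing adds error to the marker.
- **The between-arm contrast** is exposed only to a part that differs between arms: a recent-meat effect, or draw timing that differs by arm in a trial where participants and testing staff know the allocation.

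**Working it through.** The plan states no figure on this point, so there is none to reproduce.

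**1. Share of mornings after a training day.** With three training days a week (Exercise program), p = 3/7 = 0.429, or 43%. There are seven weekly patterns in which no two training days are adjacent. If draws are possible Monday to Friday only, 40% to 60% of mornings follow a training day, depending on the pattern. For Monday to Saturday it is 33% to 50%. The article does not give collection days. The 43% takes all mornings as equally likely and training as still under way at the draw. At baseline the share after a study session is 0.

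**2. Within-arm shift and added variance.** Let d be the shift in a day-after sample, in SD of the follow-up marker without timing variation. The documents give no value, so d is assumed to lie between 0.2 and 1.0.

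- Mean shift = p × d = 0.429d
- Added variance = p(1 − p)d² = 0.429 × 0.571 × d² = 0.245d²

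| d (assumed) | Mean shift (SD) | Added variance |
|---|---|---|
| 0.2 | 0.09 | 0.010 (1%) |
| 0.5 | 0.21 | 0.061 (6%) |
| 1.0 | 0.43 | 0.245 (24%) |

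**3. Between-arm contrast.** Split the shift into e (exercise, both arms) and m (additional effect of recent supplied meat, meat arm only). With the same p in both arms:

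- Meat arm: p(e + m)
- Control arm: p × e
- Difference: p(e + m) − p × e = p × m

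The exercise term drops out. Illustrations with assumed values:

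| p | e | m | Meat arm | Control arm | Difference |
|---|---|---|---|---|---|
| 0.43 | 0.5 | 0 | 0.21 | 0.21 | 0 |
| 0.43 | 0.5 | 0.2 | 0.30 | 0.21 | 0.09 |
| 1 | 0.5 | 0.2 | 0.70 | 0.50 | 0.20 |

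The last row is the extreme case in which every draw follows a training day.

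**4. Marker–cognition regression.** Suppose the follow-up marker were the only predictor and the timing shift were unrelated to cognition. The slope would then be multiplied by 1/(1 + added variance): 1/1.010 = 0.99, 1/1.061 = 0.94 and 1/1.245 = 0.80 for d = 0.2, 0.5 and 1.0.

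**5. Effect of the fix.** Training days are not adjacent, so a draw before training on a training-day morning always follows a non-training day. If the previous session and meat dinner ended by about 8 pm two days earlier (assumed), an 8 am draw is about 36 hours later. The share of draws made the morning after a session falls from 43% to 0. The documents give no clearance time, so full wash-out cannot be shown.

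**The case against.** **This is a condensed article.** Scheduling a draw around sessions is procedural detail that the full protocol may hold, and nothing in the section is wrong or contradicted. That stands, and it limits the point to a suggested improvement. The section does set out its sampling conditions, however, and as they stand they permit the variation described.

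**Both arms train.** A reader might infer that acute carry-over will be taken for a lasting treatment effect. The documents do not support this. The arms share one exercise programme, allocation is randomised, and the effect is assessed between arms, so the exercise part cancels in expectation. The 0.09 to 0.43 SD is a shift in a within-arm mean.

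**The sizes are assumed.** This stands. The article gives neither the size nor the duration of any day-after response, for exercise or for meat, and the overnight fast and fixed morning window already limit meal effects. Controls also eat some meat and fish, so the dietary difference the day before is one of degree.

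**Baseline is not exercise-free.** This also stands. Resistance exercise on up to one day a week and moderate activity under 150 minutes a week are compatible with entry. Only study sessions and study meals are absent before baseline. Nor does the article say that participants choose their draw morning.

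**Timing can partly be reconstructed.** Under Compliance, trainers log attendance at each session and supplied meat goes on a calendar. Days since the last session and serve could therefore largely be recovered for a sensitivity analysis. Hours could not, and the draw itself cannot be retimed.

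**Conclusion.** The point holds as a minor one. The draw is standardised for fasting and clock time but not for time since the last session or supplied serve. About 43% of possible week 12 and 24 mornings follow a training day (33% to 60% under the collection-day patterns considered), against none at baseline for study sessions and study meals.

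The consequence is possible distortion of within-arm change and extra noise in the secondary markers and the exploratory regression. For an assumed day-after shift of 0.2 to 1.0 SD, that is 0.09 to 0.43 SD in the follow-up mean and 1% to 24% in follow-up variance. A between-arm bias would need a recent-meat effect or draw timing that differs by arm. The documents give no size for the first and do not show the second. The DXA, pQCT, strength and cognitive primary outcomes are not affected by when blood is drawn.

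**What to change.** In the section on biochemical, hormonal and inflammatory markers, add one rule for both arms: the week 12 and week 24 samples are taken before training on the morning of a scheduled training day, so that the preceding day is a non-training day without supplied meat. The request form should record the time since the last session and, in the meat arm, since the last supplied serve, so that any remaining variation can be examined.

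The cost is one line in the appointment instructions and two form fields, with no extra visit or assay. There are two downsides. Participants have less freedom over appointment days. Urea, creatinine and eGFR would always be read after a day without supplied meat, and because the Discussion expects to show no adverse effect on kidney function, this should be stated when the kidney results are interpreted.

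For samples already collected, days since the last session and serve can be approximated from the attendance records and calendars and used in a sensitivity analysis.
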